No validated, widely applicable clinical prediction tool currently exists that integrates bedside clinical features, routine laboratory parameters, and emerging biomarkers to accurately stratify patients by severity risk, despite progress in understanding dengue pathophysiology. This gap results in significant heterogeneity in clinical decision-making ranging from unnecessary hospitalizations that strain healthcare resources to premature discharge of high-risk patients [7]. The consequences are particularly severe in resource-limited endemic settings, where intensive care capacity is constrained and case fatality rates can exceed those in well-resourced environments [8]. 

Recent advances in high-throughput multi-omics technologies have fundamentally transformed the capacity to interrogate host responses to infectious diseases. The ability to simultaneously characterize transcriptomic, proteomic, and metabolomic alterations from a single biological sample offers an unprecedented systems-level perspective on host–pathogen interactions, enabling the identification of molecular signatures that transcend single-platform observations and more faithfully capture the biological complexity underlying disease severity [9]. 

The COMBAT study aims to address this gap by employing a multidisciplinary, systems biology approach to identify molecular signatures and pathways associated with dengue severity across geographically distinct endemic regions. The identification of predictive biomarkers and mechanistic pathways may support earlier dengue risk stratification, improve clinical management, and inform the development of novel therapeutic strategies.

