### Study cohorts

Blood samples from patients are collected as per the WHO revised 2009 case classification [1] as: (1) dengue without warning signs (DwoWS), (2) dengue with warning signs (DWS) and (3) severe dengue (SD). Additionally, non-dengue samples will be collected from DENV-negative healthy controls (HCs). 100 individuals from each category will be collected in Guatemala and will serve as the discovery cohort, while 150 individuals from each category will be collected from India and serve as the validation cohort. The patient inclusion and exclusion criteria are presented in Table 1. Additional cohorts from Guatemala, Brazil and Honduras will be used for further validation of the dengue severity biomarkers. Validation of any additional cohorts requires a local ethical clearance, as well as approval from both the Swedish Ethical Review Authority and the COMBAT General Assembly.

**Table 1 Tab1:** Inclusion and Exclusion Criteria for patient enrolment

Inclusion Criteria: The criteria for enrolling the patients in the respective groups.
**Group 1**: Dengue without warning signs (DwoWS) Patients presenting with the following symptoms and confirmed positive for dengue infection following anti-dengue IgM or NS1 ELISA (Enzyme-linked Immunosorbent Assay) lab tests. Symptoms are fever along with at least two of the following: • Myalgia, arthralgia • Nausea and/or vomiting • Rashes • Leukopenia
**Group 2**: DENV with warning signs (DWS) Patients with the above symptoms and any of the following clinical signs: • Abdominal pain with tenderness • Persistent vomiting • Fluid accumulation • Mucosal bleeding • Restlessness, lethargy • Liver enlargement >2 cm • Laboratory findings: An increase in hematocrit levels and a rapid decrease in platelet count
**Group 3**: Severe dengue (SD) Patients with: • Severe plasma leakage leading to hypovolemic shock (dengue shock syndrome) and fluid accumulation with respiratory distress • Severe bleeding, such as epistaxis, and internal bleeding, evaluated by a clinician • Severe organ involvement with any of the following symptoms: - Liver AST or ALT ≥ 1000 - CNS: impaired consciousness - Heart and other organs failure
**Exclusion criteria**: Individuals with the following characteristics were not enrolled.

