• Patients below the age of 18 years • Pregnant, immunocompromised or undergoing chemotherapy, on steroids or immunosuppressive drugs in the last year or with liver cirrhosis • Co-infection with a non-dengue pathogen • Cases with a lab-confirmed dengue infection within the past three months

The study is designed to investigate the progression of dengue infection in patients, from without warning signs, to with warning signs to severe dengue, which varies between cases. If a patient recruited in the category “DwoWS” develops symptoms correlating with severity and receives intensive care, they will then be re-categorized into the second “DWS” or third “SD” group. Keeping in mind the complexity of dengue presentation, subcategorization of the patients will be performed as necessary to establish the degree of severity depending on the timepoint of recruitment and the points of sample collection. The highest (peak) severity category reached during the acute illness constitutes the participant’s definitive severity classification and serves as the primary outcome label for all biomarker analyses. For incorporation into the biomarker discovery and validation analyses, the earliest sample for each participant collected before or at the point of clinical deterioration is used as the predictor, and the definitive peak severity category is used as the outcome.

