### Study procedures

A single blood sample is collected from the non-hospitalized patients, while two blood samples per participant are collected from the hospitalized patients. The first one is taken within the first two days of hospitalization, and the second at discharge. A questionnaire is administered at the time of blood collection (Table 2). Total participation time is less than 15 min. For Guatemala, whole blood is collected in Tempus™ tube for transcriptomics and in Cytodelics medium for flow cytometry, while plasma from EDTA blood and serum are collected for proteomics, metabolomics and glycomics. For India, whole blood (3 ml) is collected in Tempus™ tubes for transcriptomics and 7–8 ml in BD Vacutainer CPT™ Cell Preparation Tubes for plasma separation and PBMC isolation.

**Table 2 Tab2:** Routine clinical investigations performed in dengue cases in all the cohorts

Parameters	Unit of Measurement
Age	In years
Sex	Male/Female

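### The primary severity label rests on two rules that disagree about intensive care, and the article describes no way of establishing peak severity for outpatients

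*Protocol article*

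**What the plan says.** All the relevant text is in the protocol article.

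- **Study cohorts, text after Table 1, re-categorization.** If a patient recruited as DwoWS "develops symptoms correlating with severity and receives intensive care, they will then be re-categorized into the second" (DWS) or third (SD) group. The sentence covers only patients recruited as DwoWS.
- **Same paragraph, outcome label.** "The highest (peak) severity category reached during the acute illness constitutes the participant’s definitive severity classification and serves as the primary outcome label". This applies to every biomarker analysis. The predictor paired with it is each participant's earliest sample taken before or at deterioration.
- **Table 1, DWS.** "Patients with the above symptoms and any of the following clinical signs", followed by a list of clinical and laboratory warning signs. SD is defined by severe plasma leakage, severe bleeding or severe organ involvement. Neither definition mentions where or how the patient is treated.
- **Study procedures.** "A single blood sample is collected from the non-hospitalized patients, while two blood samples per participant are collected from the hospitalized patients"; the hospitalized patients are sampled within two days of admission and again at discharge. The questionnaire accompanies the blood draw.
- **Background.** The febrile phase is placed on days 1–3 and the critical phase on days 4–6.
- **Primary endpoints.** One is a validated panel that predicts progression to severe dengue.

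**The concern.** The label is the dependent variable of every biomarker analysis, so its rule has to give one answer per patient. Here a treatment received (intensive care) enters one rule and is absent from the other and from Table 1. Where the first rule is applied, the label partly records care received and not disease severity alone.

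The second difficulty concerns ascertainment. A peak can be known only if the patient is observed through the period in which the peak occurs. For an outpatient sampled in the febrile phase, the procedures described record a category before the critical phase and nothing after it.

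Both problems act on the same patients. Those sampled early and mild who later worsen are the informative cases for a prognostic panel. If their worsening is not recorded, they sit in the mild comparison group and dilute the contrast that the study is meant to find.

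**Working it through.** **1. The labelling rules side by side**

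| Patient recruited as | Later course | Re-categorization sentence | Peak-severity sentence with Table 1 |
|---|---|---|---|
| DwoWS | warning signs, intensive care | moved to DWS or SD | DWS or SD by criteria met |
| DwoWS | warning signs, ordinary ward | condition not met; can stay DwoWS | DWS |
| DwoWS | SD criteria met, no intensive care | condition not met; can stay DwoWS | SD |
| DWS | SD criteria met | not addressed | SD |

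The rows agree only when intensive care is given.

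**2. What is recorded for an outpatient**

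One sample and one questionnaire at that sample. If the sample falls on days 1–3, the whole critical phase (days 4–6) lies after the only described data capture. The data management section lists longitudinal outcome data but does not say how these are obtained for outpatients.

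**3. The plan's own sample size, reproduced**

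Inputs from Statistical analysis: 20,000 genes, 100 prognostic, fold change 2, control mean count 5, dispersion 0.5, normalization ratio 1, FDR 0.01, power 0.8.

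- Per-gene alpha: 100 × 0.8 × 0.01 / (19,900 × 0.99) = 4.06 × 10⁻⁵, two-sided, critical value 4.104.
- An exact negative-binomial two-group test (mean 5 against 10) gives power 0.793 at 66 per group and 0.804 at 67. The stated 67 is reproduced.
- Wald check: variance term 1/5 + 1/10 + 2 × 0.5 = 1.3; n = 1.3 × (4.104 + 0.842)² / (ln 2)² ≈ 66.2.
- Loss: 67 / 0.7 = 95.7, so 96; enrolling 100 leaves 70 usable.

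**4. Illustration of dilution (q is assumed, not in the documents)**

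Let a share q of the group labelled DwoWS be unrecognized progressors with the same mean count as the severe group. The mild mean becomes 5(1 + q) and the observed fold change 10 / [5(1 + q)] = 2/(1 + q). Alpha and dispersion are held fixed.

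| q | Fold change | Exact power, 67 per group | Exact power, 70 per group |
|---|---|---|---|
| 0 | 2.00 | 0.80 | 0.83 |
| 5% | 1.90 | 0.70 | 0.73 |
| 10% | 1.82 | 0.58 | 0.61 |
| 20% | 1.67 | 0.34 | 0.37 |

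Wald check at q = 10%, 67 per group: variance term 1/5.5 + 1/10 + 1 = 1.282; ln 1.818 / √(1.282/67) − 4.104 = 0.22, power about 0.59, in line with the exact 0.58.

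**The case against.** The strongest reply is that the re-categorization sentence gives a sufficient condition, not an exclusive one. It does not say that patients move *only* if they receive intensive care, and the peak-severity sentence, being general and expressly about the outcome label, can be read as governing all cases, including DWS to SD. That reading is available, and on it the defect is loose wording. But the sentence with the intensive-care condition is the only operational instruction given for moving a patient, and it attaches that condition even to a move to DWS, which Table 1 defines by warning signs alone. Sites following it can label the same patient differently from sites following the general sentence. The conflict therefore stands, although *can remain* DwoWS is as far as it goes.

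Three stronger readings are tempting and are not supported:

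- **That outpatients are not observed after a contact of under 15 minutes.** The sentence "Total participation time is less than 15 min" is not limited to outpatients. It stands in a paragraph that also covers patients sampled again at discharge, so it most naturally means procedure time. Absence of follow-up is an inference from a condensed article; no sentence excludes it, and an outpatient later admitted to a study hospital could be caught.
- **That the label varies with bed availability between sites or countries.** The Background phrase "where intensive care capacity is constrained" describes resource-limited endemic settings in general. Nothing compares intensive-care capacity between the study sites.
- **That a known amount of power is lost.** The documents give no progression rate, mislabelling rate or outpatient share of the DwoWS group. The sample-size text speaks of a control group without naming DwoWS; if healthy controls are meant, the dilution does not touch that contrast.

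**Conclusion.** The point holds. The article states two rules for the primary outcome label that disagree whenever a patient worsens without intensive care, and the re-categorization rule is silent on DWS to SD. Separately, the procedures described for outpatients cannot establish a peak category when sampling precedes the critical phase, so progressors can stay in the mild group. The first part rests on the text alone. The second rests on what the article describes and would fall away if the full protocol specifies outcome ascertainment for outpatients.

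The size of the effect is unknown. The fall in power from 0.80 to about 0.58 or 0.34 is illustrative: it assumes 10% or 20% of the DwoWS group are progressors who resemble the severe group, unchanged dispersion, and a contrast that uses DwoWS. It shows that modest mislabelling would matter, not that it occurs.

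**What to change.** These changes concern the research outcome label only, not patient care.

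1. Reconcile the re-categorization sentence with Table 1: remove the intensive-care condition from the label and assign the peak category from Table 1 criteria at every recorded assessment, for all transitions including DWS to SD.
2. State how peak category is ascertained for non-hospitalized patients: a record check or brief contact after the critical phase.
3. For participants already enrolled (170 across the four groups in Guatemala as of June 2026), use existing records. Where that is impossible, mark the label as severity at sampling.
4. Repeat the main analysis excluding outpatients whose peak was not ascertained. Limiting it instead to outpatients first sampled after day 6 would not serve: it would set recovery-phase samples against early hospital samples and confound severity with illness phase.

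The cost is one reworded sentence, a small amount of record checking, and some outpatients left out of the sensitivity analysis. With recruitment planned to run until November 2027 and the India cohort starting only in July 2026, most of the ascertainment can still be done prospectively in that cohort.

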#### Multi-omics studies and biomarker identification

We will perform RNA sequencing (RNA-seq) of the blood cells [10], proteomics by Olink^®^ Reveal, and metabolomics using liquid chromatography-mass spectrometry (LC-MS/MS) in the samples collected from Guatemala [11, 12]. Due to different numbers of analytes, i.e., genes from RNA-seq (n = ~ 20000), protein (n = ~ 1034) and metabolites (n = ~ 1200), we will first identify biomarkers associated with disease severity in each omics dataset using Random Forest for feature selection, and Bayesian belief network (BBN) based structural causal modelling to infer putative causal relationships [12]. To further refine the biomarkers, we will perform integrative analysis using the Consensus Association (CA) analysis and gene/protein/metabolite cooperation networks by integrating the transcriptomics, proteomics and metabolomics analysis to identify a robust mechanism-informed protein biomarker panel for clinical translation [9]. Additionally, a high-throughput analysis of total plasma, IgG, and/or IgM N-glycome [13, 14] from the available patient cohorts will be performed to evaluate glycosylation as a biomarker of disease severity. For Indian samples we will perform RNA-seq of the blood cells and proteomics by Olink^®^ Reveal.

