#### Artificial intelligence (AI) models for DENV severity

The assessment of DENV severity using traditional methods has proven difficult due to many contributing factors, such as variation in symptoms, dynamic nature of dengue infection, and lack of specific biomarkers, amongst others [8]. Multiple machine-learning and deep-learning models, including logistic regression, random forests, XGBoost, support vector machines, multilayer perceptrons, and multimodal neural-network architectures, will be trained and systematically compared for DENV severity prediction. The models will integrate available clinical, laboratory, demographic, virological, and multi-omics data, using feature-selection and dimensionality-reduction approaches. Model interpretability will be assessed using explainable AI approaches, including SHapley Additive exPlanations (SHAP) and Local Interpretable Model-agnostic Explanations (LIME), to identify the variables and molecular features driving individual- and cohort-level predictions. Temporal and geographical robustness will be evaluated using time-split validation, external validation across sites, and leave-one-site-out cross-validation. Model performance will be assessed using AUROC, AUPRC, sensitivity, specificity, F1-score, calibration, and decision-curve analysis to identify clinically robust and generalizable models for DENV severity prediction.

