### Study endpoint

#### Primary endpoints

Multi-omic (transcriptomic, proteomic, metabolomic and glycomic) signatures that differ significantly across dengue severity categories.A validated multi-omics-derived host biomarker panel that predicts progression to severe dengue.

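### The outcome set for all biomarker analyses is the three-level peak severity category, but the second primary endpoint is progression to severe dengue, and the article does not map one to the other.

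*Protocol article*

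**What the plan says.** The protocol article, Study cohorts, recruits dengue patients in three WHO 2009 categories (DwoWS, DWS, SD), with 100 per category in Guatemala (discovery) and 150 per category in India (validation). The text after Table 1 settles which category counts when a patient deteriorates. The peak category is the "definitive severity classification and serves as the primary outcome label for all biomarker analyses". For both discovery and validation, the predictor is the earliest sample taken before or at deterioration, "and the definitive peak severity category is used as the outcome".

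Primary endpoints lists two items. The first is multi-omic "signatures that differ significantly across dengue severity categories". The second is "A validated multi-omics-derived host biomarker panel that predicts progression to severe dengue".

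Multi-omics studies and biomarker identification says the study will "identify biomarkers associated with disease severity in each omics dataset using Random Forest for feature selection", without naming a contrast. The AI models section adds: "Model performance will be assessed using AUROC, AUPRC, sensitivity, specificity, F1-score, calibration, and decision-curve analysis". It does not say whether these are computed for two classes or three. The Flex panel section limits the final panel to 5–10 proteins.

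**The concern.** The first primary endpoint fits a three-level label. The second is a yes/no event and does not fit it without a further step. A DWS patient is a non-event for progression to SD but a class of its own under the labelling rule. By quota that is one third of the dengue patients: 100 of 300 in Guatemala and 150 of 450 in India.

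Two things are left open. The first is the contrast. If selection uses all three levels, a protein that marks the step from DwoWS to DWS can take a panel place although that step is not part of the endpoint. The second is the risk set. Table 1 allows enrolment directly as SD, and the predictor sample may be taken at deterioration. A peak label of SD therefore does not by itself show that the patient progressed after sampling.

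At stake is whether the panel claimed for the second primary endpoint actually identifies who becomes severe.

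**Working it through.** **Plan's own figure.** The only sample-size figure is for a generic two-group RNA-seq comparison. Per-gene alpha = (0.8 × 100 × 0.01) / (19,900 × 0.99) = 4.06 × 10⁻⁵. An exact negative-binomial test (means 5 and 10, dispersion 0.5) has power 0.793 at 66 and 0.804 at 67 per group, so the stated 67 is reproduced. 67 / 0.7 = 95.7, so 96, which 100 covers. This figure does not bear on the panel's outcome.

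**Bounding case.** Take a panel that separates DwoWS perfectly and carries no SD-versus-DWS information, with equal groups.
- Mean pairwise AUROC = (1 + 1 + 0.5) / 3 = 0.83
- SD versus not SD = (1 + 0.5) / 2 = 0.75
- SD versus DWS = 0.50

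**Single marker.** Assumptions: normal marker with standard deviation 1; 70 per group (100 × 0.7); alpha 0.05 / 1034; 3,000 runs. AUROC = Φ(difference / √2).

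| Means DwoWS/DWS/SD | Selected, three-group test | Selected, SD v not SD | AUROC SD v DWS |
|---|---|---|---|
| 0 / 1 / 1 | 99% | 15% | 0.50 |
| 0 / 0 / 1 | 99% | 99.5% | 0.76 |
| 0 / 0.5 / 1 | 92% | 81% | 0.64 |

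**Panel of 8.** Assumptions: 1034 proteins, of which 20 mark DwoWS versus the rest and 20 mark SD versus the rest; within-block correlation 0.3; 70 per group in discovery and 105 (150 × 0.7) in validation; 200 replicates. The top 8 are chosen by a three-group F statistic or by an SD-versus-rest t statistic. The same SD-versus-not-SD discriminant is then fitted to both panels, so only the selection label differs. Cells show three-level against binary selection.

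| Effects, DwoWS boundary / SD | AUROC SD v not SD | AUROC SD v DWS |
|---|---|---|
| 1.0 / 0.6 | 0.68 v 0.76 | 0.51 v 0.70 |
| 0.8 / 0.6 | 0.69 v 0.75 | 0.58 v 0.72 |
| 0.6 / 0.6 | 0.72 v 0.74 | 0.68 v 0.73 |
| 0.6 / 0.8 | 0.809 v 0.811 | 0.799 v 0.812 |
| 0.4 / 0.6 | 0.739 v 0.743 | 0.731 v 0.742 |
| Graded markers 0/0.4/0.8 | 0.737 v 0.738 | 0.669 v 0.670 |

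The last three rows come from a repeat of the design with a separately chosen ridge penalty. At 0.8/0.6 that repeat again gave 0.69 against 0.75 for SD versus not SD.

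At 0.8/0.6, DwoWS-boundary proteins take 86% of places under three-level selection and 9% under binary selection. At 1.0/0.6 the mean pairwise AUROC is slightly higher for the worse panel (0.735 against 0.716). With Random Forest importance, the method the article names (40 replicates), the 0.8/0.6 setting gives 75% against 10% of places and SD-versus-DWS AUROC 0.64 against 0.72. At 0.6/0.6 it gives 0.68 against 0.72.

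**Risk set.** Let s be the share of SD patients already severe at the predictor sample. The article does not give s. Events left for a progression analysis = N × (1 − s). Before any sample loss, s = 0.25, 0.50 and 0.75 leave 75, 50 and 25 of 100 in Guatemala, and 112.5, 75 and 37.5 of 150 in India.

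**The case against.** A reader might infer that the panel is selected on one question and validated on another. The text does not say that: the same peak label is set for discovery and for validation. The mismatch is between that label and the wording of the second primary endpoint. Nor is there a flat contradiction. SD is one level of the label, so SD versus not SD can be derived from it, and one peak label can serve both primary endpoints.

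A reader might also infer that a three-level AUROC or a multiclass selection step is planned. No section prescribes either. The Flex panel section and the Discussion both point the panel at severe dengue, and most of the listed performance measures are two-class, which suggests that a binary contrast may be intended.

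The large losses above also need DwoWS-boundary effects stronger than SD effects. With graded markers, natural for an ordered disease course, the loss almost vanishes, and a single graded marker is selected more often by the three-group test (92% against 81%).

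All of this stands and limits the point. It does not remove it. The article does fix an outcome, for every biomarker analysis, so this is more than a detail left to an analysis plan. A plan that used SD versus not SD for the panel would have to add a step the article does not state. Deriving that contrast only at scoring would not undo a selection already made on three levels.

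**Conclusion.** The stated outcome for biomarker analyses does not match the second primary endpoint, and the article gives no mapping between them. The risk is real but its size is unknown. The bounding values (0.83, 0.75, 0.50) are exact arithmetic for an extreme panel. The simulated loss in SD-versus-DWS AUROC runs from 0.001 (graded markers) to 0.19 (effects 1.0/0.6), under assumed effects, correlation and panel size. In none of the panel settings did the binary target give a lower AUROC for SD. The simulation leaves out the later causal-network and integration steps of the article's pipeline.

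A binary contrast alone is not enough. Patients already severe when sampled would still count as events, and the uninformative panel of the bounding case would still score 0.75. The risk set and the SD-versus-DWS figure are needed as well. This should be corrected, and it does not undermine the design.

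**What to change.** Keep the three-level peak label for the first primary endpoint. For the second, state the following in Study cohorts, in Multi-omics studies and biomarker identification, and in the AI models section:

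- Panel feature selection, training and headline validation use peak SD versus not SD (DwoWS plus DWS), among participants who do not yet meet the SD criteria at the predictor sample.
- Participants already severe at that sample are analysed separately.
- The SD-versus-DWS AUROC is reported beside the headline figure in both cohorts.
- Three-level or ordinal models are secondary.

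This is a wording change plus one extra contrast, with no new patients or samples. It needs severity status recorded at the time of the predictor sample. There are two costs: fewer SD events in the headline analysis, by a share that should be counted early, and a headline panel that makes no claim to predict DWS. Study status reports 170 participants enrolled in Guatemala by June 2026 and Indian recruitment starting in July 2026, so the target can still be fixed before validation data are available.
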